#### 2.4.2. Exclusion Criteria

The exclusion criteria are as follows: (1) received pacemaker surgery, coronary intervention, or coronary artery bypass surgery or have other metal products in the body; (2) language dysfunction caused by congenital or childhood diseases; (3) language dysfunction caused by mental disturbance and normal mental retardation; (4) severe dysarthria and hearing impairment; (5) superficial sensation abnormalities in the neurological examination, and (6) participation in other studies.

### 2.5. Interventions

Acupuncture will be performed by registered acupuncturists with over 2 years of experience who will be trained in the standardization of the acupuncture scheme. Only sterile, stainless steel, disposable acupuncture needles (size 0.25 mm × 40 mm, product no. 20182270011; ANDE Acupuncture, Guizhou ANDE Medical Equipment, China) will be used. Both acupuncture and sham acupuncture points will be located in the limbs and head. All the participants will receive 3 treatment sessions per week (alternate days) for 4 consecutive weeks, resulting in a total of 12 sessions. Each treatment will be administered for 30 minutes. The acupuncture and sham acupuncture interventions will be performed by a consensus of acupuncture experts. To ensure strict adherence to the study protocol, the experts will receive training together and use the same techniques. The details of the acupuncture treatment are described in the Standards for Reporting Interventions in Clinical Trials of Acupuncture (STRICTA [39]) checklist in Table 3.

#### 2.5.1. Acupoint Group

Participants in the acupoint group will receive acupuncture at bilateral Tongli (HT5) and Xuanzhong (GB39) limb acupuncture points. After skin disinfection, acupuncture needles will be inserted through the skin and approximately 0.5 cun [≈10 mm] into the skin. Needle insertion will follow an angle of 90° in an inferomedial direction for the two points. Following needle insertion, small, equal manipulations of twirling and thrusting will be performed on all needles to reach de qi (a composite of sensations including numbness, distention, soreness, and heaviness that is an important indicator of successful acupuncture treatment), which is believed to be an essential component for acupuncture efficacy. The needles placed in HT5 and GB39 will be manually stimulated every 10 minutes. The acupuncture points on the head are Lianquan (RN23), Jinjin (EX-HN12), Yuye (EX-HN13), Baihui (DU20), and Sishencong (EX-HN1). For RN23, acupuncture needles will be inserted through the skin and approximately 1 cun [≈20 mm] into the skin. Following needle insertion, small, equal manipulations will be performed on the needles to reach numbness. EX-HN12 and EX-HN13 will be quickly inserted for bloodletting. DU20 and EX-HN1 will be inserted through the skin approximately 0.5 cun. Needle insertion will follow an angle of 15° in an inferomedial direction for the two points (for details, see Table 4 and Figure 2).

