### 2.3. Setting and Recruitment

Participants who meet the inclusion and exclusion criteria will be recruited from the inpatients in the Dongzhimen Hospital affiliated to Beijing University of Chinese Medicine (BUCM), China Rehabilitation Research Center, and Peking University Third Hospital. Participating institutions and the level of the institution are listed in Table 2. The study will be advertised through the Internet and posters in communities and hospitals. The inpatients and potential participants will call an investigator and be prescreened for eligibility and will learn how to participate in this clinical trial through visits or telephone calls to our hospital. During visits to the clinical research centre of Dongzhimen Hospital affiliated to BUCM, China Rehabilitation Research Center, and Peking University Third Hospital, the accessors will explain the study to the patients, who will be asked to sign an informed consent form before voluntary participation. The participants of this study will be selected from the applicants who meet all the inclusion criteria but do not meet any of the exclusion criteria. To facilitate participation in this study, the accessors will properly adjust the evaluation and treatment schedule of the enrolled participants. Therefore, the enrolled participant will be able to complete the treatment and evaluation. Every time the enrolled participant visits, the accessors will inform the participant of the next scheduled visit, and the day before the visit, the accessors will remind the enrolled participant of the schedule by telephone.

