### 2.4. Eligibility Criteria

#### 2.4.1. Inclusion Criteria

Participants meeting all of the following criteria will be included in this trial: (1) diagnosed as stroke through computed tomography (CT) or MRI, 1 to 6 months after stroke onset; (2) 30 to 80 years of age (After the expert discussion and the actual situation of our country, the age range has been adjusted), the native language is Chinese, and right-handed; (3) primary school and above education with no serious heart, liver, or kidney diseases; (4) clear consciousness and no cognitive impairment; (5) normal language function before the stroke onset and dominant language dysfunction with mild limb dysfunction; (6) specific aphasia syndrome diagnosed as motor aphasia by the WAB; (7) BDAE score of 2 to 4; and (8) able to cooperate for the 30-minute MRI examination.

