#### 2.5.2. NA Control Group

Participants in the NA control group will receive sham acupuncture with real needles on an NA. NA 1 will be 0.5 cun (≈10 mm) lateral to HT5. NA 2 will be 0.5 cun (≈10 mm) horizontal to GB39, and NA 3 will be 0.5 cun (≈10 mm) lateral to ST8 (for details, see Table 5 and Figure 3). Procedures and other treatment settings will be the same as in the acupoint group but with no needle manipulation for de qi. In both groups, the needles will be retained for 30 minutes for each treatment session. The participants will be treated with acupuncture three times a week, on alternate days, for 4 successive weeks, resulting in a total of 12 sessions for each patient.

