#### 2.8.4. Quality Control

All practitioners will conduct the study according to the standard operating procedure of the study. We will conduct several simulations for our volunteers before the start of the study. During the study, regular meetings will be held to discuss issues raised by researchers or participants, the need to improve protocols, the side effects, and participant recruitment.

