## 3. Discussion

PSA has proven to be difficult to treat. There is a degree of spontaneous recovery in the subacute phase, so there are few studies on the subacute phase of PSA. However, the subacute phase also requires treatment. The extant literature shows that acupuncture is probably effective for PSA [18, 45–47]. We intend to evaluate the long-term efficacy of acupuncture in maintaining speech production function. One common problem is the lack of standardization of acupoint selection, needle retention time, number of needles used, needling depth, and needle manipulation in acupuncture research.

From 2006 to now, we attempted to explore the general acupuncture scheme based on syndrome differentiation. In our PSA acupuncture treatment programme, DU20 is located in the area at the top of the head and is particularly closely related to the regulation of brain speech activity. The EX-HN1 are the acupuncture points around the DU20, both of which are used together to benefit the brain and promote speech rehabilitation. The treatment of PSA by EX-HN12 and EX-HN13 bloodletting has a theoretical basis in TCM and unique clinical efficacy. CV23 is mainly used for the treatment of speechlessness, stabbing into the skin towards the root of the tongue, and has the effect of restoring speech. The acupuncture theory of HT5 and GB39 to be used in our study is different from the traditional meaning of these points. FMRI can help us evaluate the changes of needle-related neuroplasticity, so we have conducted fMRI experiments based on this pair of effective points for aphasia. Electroacupuncture at HT5 and GB39 may modulate language and cognition function through a complex network formed by an extensive area of the brain cortex. It is beneficial to the recovery of language function [47]. In previous studies, we have demonstrated that this acupuncture protocol has shown significant improvements in auditory comprehension, reading, and dictation in patients with subacute PSA after 4 weeks of treatment. Therefore, we would like to know more about whether this treatment programme has long-term effects in these areas and observe the association with overall linguistic changes.

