**Figure 4 fig4:**
[figure not shown]
MRI experimental paradigm and an illustrative diagram of the word-picture judgement task. For fMRI, there were 60 blocks. For ERP, 60 blocks. When presenting the task, the word is displayed in Chinese.

**Table 1 tab1:** Study design schedule.

Period	Screening and baseline	Treatment (w1–4)				Follow-up (w5–12)	Follow-up (w13–24)
Week (W)	W −1	W1	W2	W3	W4	W12	W24
Eligibility	×						
CT or MRI	×						
General information	×						
Physical examination	×				×	×	×
Medical history and demography	×						
Informed consent	×						
WAB		×			×	×	×
BDAE		×			×	×	×
Disease Prognosis Scale of ischaemic stroke		×			×	×	×
MRI (3D-T1, RS-fMRI, Task-fMRI, DTI)		×			×	×	×
EEG		×			×	×	×
ERP		×			×	×	×
Discomfort and acceptance of acupuncture		×	×	×	×	×	×
Assessment of blind method		×					
Adverse event			×	×	×	×	×
Compliance			×	×	×	×	×

CT, computed tomography; MRI, magnetic resonance imaging; WAB, Western Aphasia Battery; BDAE: Boston Diagnostic Aphasia Examination; RS-fMRI, resting-state functional magnetic resonance imaging; DTI, diffusion tensor imaging; EEG, electroencephalogram; ERP, event-related potentials.

**Table 2 tab2:** List of participating institutions and level of the institution.

Participating centre	Level of the institution
Dongzhimen Hospital Affiliated to Beijing University of Chinese Medicine	Tertiary A hospital
China Rehabilitation Research Center	Tertiary A hospital
Peking University Third Hospital	Tertiary A hospital

**Table 3 tab3:** Revised standards for reporting intervention in clinical trials of acupuncture (STRICTA [39]]).

Item	Item criteria	Description
(1) Acupuncture rationale	(1a) Style of acupuncture	Traditional Chinese medicine therapy
	(1b) Reasoning for treatment provided, based on historical context, literature sources, and/or consensus methods, with references where appropriate	(i) Reasoning for treatment provided—based on historical context, literature sources, and traditional Chinese medicine (consensus) (ii) Reasoning for treatment provided—based on historical context, literature [27,28], selection of treatment regions based on related papers, expert experience, and textbooks
	(1c) Extent to which treatment varied	Standardized treatment
(2) Details of needling	(2a) Number of needle insertions per subject per session (mean and range where relevant)	10 or 12

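### The acupoint arm includes bloodletting at the veins under the tongue, yet no eligibility criterion bars a patient with a known bleeding disorder or known low platelets

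*Protocol article*

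**What the plan says.** **Procedure.** Section 2.5.1 states that "EX-HN12 and EX-HN13 will be quickly inserted for bloodletting", and Table 3 (item 2c) repeats it. The Discussion treats it as an intended part of the therapy: "The treatment of PSA by EX-HN12 and EX-HN13 bloodletting has a theoretical basis in TCM and unique clinical efficacy". Table 4 locates EX-HN12 and EX-HN13 on the veins to the left and right of the tongue frenulum. Section 2.5 sets 12 sessions over 4 weeks.

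**Control arm.** Section 2.5.2 says: "Participants in the NA control group will receive sham acupuncture with real needles on an NA". The three sites, listed there and in Table 5, lie beside HT5, GB39 and ST8. None is under the tongue and none involves bloodletting.

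**Eligibility.** Section 2.3 draws participants from "applicants who meet all the inclusion criteria but do not meet any of the exclusion criteria". The only general organ-disease criterion is inclusion item 3: "primary school and above education with no serious heart, liver, or kidney diseases". Exclusion item 1 concerns cardiac procedures and metal: "received pacemaker surgery, coronary intervention, or coronary artery bypass surgery or have other metal products in the body". The other exclusions cover language dysfunction of congenital, childhood or mental origin, severe dysarthria and hearing impairment, abnormal superficial sensation, and participation in other studies.

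**Screening.** Table 1 lists "Medical history and demography" at the screening and baseline visit.

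**The concern.** Ordinary needling may cause bleeding by accident. Here bleeding is the intended effect, at a vein inside the mouth, and it may be repeated over 4 weeks. A known bleeding or coagulation disorder, or a known low platelet count, is an obvious reason to keep a patient away from that procedure, and it can be found before randomisation. If the eligibility lists do not mention it, such a patient can be randomised. With 1:1 allocation, that patient has an even chance of receiving the bloodletting.

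What is at stake is the safety of individual participants, in one arm only. The estimand, the analysis and the power are not affected.

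**Working it through.** **Step 1: do the lists cover bleeding risk?** The article states no figure to reproduce, so the check is a reading of every criterion.

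| Source | Items | Items naming a bleeding or coagulation disorder or low platelets |
|---|---|---|
| Section 2.4.1, inclusion | 8 | 0 |
| Section 2.4.2, exclusion | 6 | 0 |

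The nearest item is the bar on serious heart, liver or kidney disease. It removes a clotting problem only when that problem accompanies serious disease of one of those organs. A primary bleeding disorder, or low platelets alone, passes all 14 items.

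**Step 2: do the lists decide entry?** Section 2.4.1 says that those who meet all its criteria will be included. Section 2.4.2 introduces its six numbered items as the exclusion criteria, not as examples. Section 2.3 selects from applicants who satisfy both lists. Medical history is taken at screening, but no criterion says that a bleeding disorder found there bars entry.

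**Step 3: exposure per patient.** Inputs: 2 sublingual points (Section 2.5.1) and 12 sessions (Section 2.5).

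- Acupoint arm, if bloodletting is done every session: 2 x 12 = 24 punctures.
- Control arm: 0.

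The 24 is an upper bound. Table 3 (item 2a) gives 10 or 12 insertions per session. The points other than the sublingual pair add up to 1 (DU20) + 4 (EX-HN1) + 2 (HT5, bilateral) + 2 (GB39, bilateral) + 1 (CV23) = 10, and the pair brings this to 12. The lower count could therefore mean sessions without bloodletting, although the article does not say so.

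**Step 4: how many patients might be affected?** Input: 24 acupoint patients (Section 2.6). The prevalence *p* among otherwise eligible candidates is not in the article, so 1% to 5% is an assumption. The expected number is 24 x *p*, and the chance of at least one is 1 - (1 - *p*)^24.

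| Assumed *p* | Expected number in acupoint arm | Chance of at least one |
|---|---|---|
| 1% | 24 x 0.01 = 0.24 | 1 - 0.99^24 = 0.214 |
| 5% | 24 x 0.05 = 1.2 | 1 - 0.95^24 = 0.708 |

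These are chances of enrolling such a patient, not of harming one. The needle is fine (0.25 mm, Section 2.5) and the article gives no bleeding rate, so harm per puncture is not estimated.

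**The case against.** The strongest case against the point has four parts.

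- **Selection wording.** Section 2.3 says participants are selected from those who meet the criteria. This can be read as making the lists necessary but not sufficient, with clinical judgement still free to turn a patient away. That reading does not survive Section 2.4.1, which says that those meeting all the criteria will be included.

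- **A condensed article.** A contraindication specific to bloodletting might sit in the full protocol or in the operating procedure, since "All practitioners will conduct the study according to the standard operating procedure of the study". This stands in part. The procedure may well govern how bloodletting is handled, so nothing is claimed here about treatment rules. But it governs conduct rather than who is eligible, and the article presents its exclusion list as complete.

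- **Existing safeguards.** Candidates are recruited from inpatients at tertiary hospitals, history and physical examination are taken, acupuncturists are registered and trained, and haematoma is a named adverse event (Section 2.8.3). These lower the residual risk. Recording a haematoma afterwards is not screening, however, and the history has no criterion attached to it.

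- **The size rests on an assumption.** This is correct. At a prevalence of 0.5% the chance of at least one such patient in the acupoint arm is 1 - 0.995^24 = 11%, and at 0.1% it is 1 - 0.999^24 = 2.4%. The finding itself rests on the eligibility lists and holds at any of these values.

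**Conclusion.** The concern holds. The article fixes bloodletting at two sublingual veins in one arm, and its eligibility lists admit a patient with a known bleeding disorder or known low platelets. Neither the organ-disease criterion nor the unseen operating procedure changes that.

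The priority is low: this is a cheap safety improvement and not a flaw in the comparison. The 21% to 71% figure depends entirely on the assumed 1 to 5% prevalence, and the count of 24 punctures depends on bloodletting at every session. Confidence is medium, because a fuller protocol that is not shown could contain the missing exclusion.

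**What to change.** Add one item to Section 2.4.2: *known bleeding or coagulation disorder, or known low platelet count*, checked from the medical history already taken at screening (Table 1).

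This needs an amendment of one line and no new test or visit. The price is a few more screen failures. At the assumed 1% prevalence, 48 / 0.99 = 48.5, so 49 otherwise eligible candidates are needed to enrol 48 (1 more). At 5%, 48 / 0.95 = 50.5, so 51 are needed (3 more).

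The item deliberately leaves out antithrombotic medication. Section 2.1 permits stroke medication without naming agents, and handling it during bloodletting may belong to the operating procedure.

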#### 2.5.2. NA Control Group

Participants in the NA control group will receive sham acupuncture with real needles on an NA. NA 1 will be 0.5 cun (≈10 mm) lateral to HT5. NA 2 will be 0.5 cun (≈10 mm) horizontal to GB39, and NA 3 will be 0.5 cun (≈10 mm) lateral to ST8 (for details, see Table 5 and Figure 3). Procedures and other treatment settings will be the same as in the acupoint group but with no needle manipulation for de qi. In both groups, the needles will be retained for 30 minutes for each treatment session. The participants will be treated with acupuncture three times a week, on alternate days, for 4 successive weeks, resulting in a total of 12 sessions for each patient.

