Regarding the study design, we developed an assessor- and participant-blinded design to minimize bias. The specific effects are thought to be generated by needling the acupoint with the appropriate manipulation. The nonspecific effects are due to other aspects of the therapy, such as the expectations of the patient, which might influence the treatment outcome. To recognize the specific effects, a placebo is needed. Among acupuncture research, placebo controls for acupuncture studies have been difficult to select. To maximally exclude the placebo effect, rigorous methodological designs are followed. In our study, control conditions involve being punctured with real acupuncture needles at NA locations. Thus, the self-perception of placebo effects in the NA control group is difficult to distinguish from the real acupoints. Additional needle manipulations will not be used in the NA control group. De qi is a characteristic constellation of sensations felt by patients during acupuncture needling. It has been regarded as an important factor related to clinical effects; however, we do not pursue this kind of sensation in the NA control group. By following these methods, participants can be successfully blinded, and the efficacy of acupuncture could be confirmed if the results of the acupoint group prove superior to those of the NA control group.

We will assess patients with PSA on multiple levels, including multiple neuropsychological tests, functional and structural brain alterations, and TCM syndrome evaluation. This multidomain assessment will be used to identify possible biomarkers involved in the effects of acupuncture in PSA.

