	(6b) Precise description of the control or comparator; details for items 1–3 with the use of sham acupuncture or any other type of acupuncture-like control	Participants in the nonacupoint control group received sham acupuncture with a pragmatic placebo needle on a sham acupoint. The needles used are the same as the acupoint group. Procedures and other treatment settings will be the same as in the acupoint group but with no needle manipulation for de qi

**Table 4 tab4:** Location of acupoints used in the acupuncture group.

Acupoints	Location
DU20 (Baihui)	On the median line of the head, 5 cun superior to the anterior hairline, at about the middle on the connecting line between the two auricular tips
EX-HN1 (Sishencong)	On the vertex, 1 cun from the front, back, left, and right to DU20 (Baihui), common 4 points
HT5 (Tongli)	On the palmar side of the forearm, 1 cun superior to the transverse crease of the wrist, at the radial border of the ulnar carpal flexor muscular tendon
GB39 (Xuanzhong)	On the lateral side of the leg, 3 cun directly above the tip of lateral malleolus at the anterior border of the fibula
EX-HN12 (Jinjin)	In the mouth, EX-HN12 (Jinjin) is located with tongue furled, on the vein on the left side of the frenulum of the tongue
EX-HN13 (Yuye)	EX-HN13 (Yuye) is located on the vein on the right side of the frenulum of the tongue
CV23 (Lianquan)	In the neck, on the anterior midline, above the laryngeal protuberance, in the depression of the superior border of the hyoid bone

**Table 5 tab5:** Location of sham acupoints used in the NA group.

Nonacupoint (NA)	Location
NA 1	0.5 cun lateral to HT5 (Tongli)
NA 2	0.5 cun horizontal to GB39 (Xuanzhong)
NA 3	0.5 cun lateral to ST8 (Touwei)

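### The control is described as the same procedure without de qi, but it has no tongue or neck counterpart and fewer needles, so superiority would support the whole programme over a reduced sham, not an isolated acupoint effect over placebo

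*Protocol article*

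**What the plan says.** **Control arm.** After listing the sham sites, Section 2.5.2 says: "Procedures and other treatment settings will be the same as in the acupoint group but with no needle manipulation for de qi". Table 3 item 6b repeats the statement. The sites are "NA 1 will be 0.5 cun (≈10 mm) lateral to HT5" and "NA 2 will be 0.5 cun (≈10 mm) horizontal to GB39, and NA 3 will be 0.5 cun (≈10 mm) lateral to ST8". Table 5 lists the same three and no others. Section 2.5 adds: "Both acupuncture and sham acupuncture points will be located in the limbs and head".

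**Acupoint arm.** Section 2.5.1 gives bilateral HT5 and GB39 with manual stimulation every 10 minutes, DU20 and EX-HN1 on the scalp, and a needle about 20 mm deep at RN23 (called CV23 elsewhere). It also states: "EX-HN12 and EX-HN13 will be quickly inserted for bloodletting". Table 4 puts the first of these two points as follows: "In the mouth, EX-HN12 (Jinjin) is located with tongue furled, on the vein on the left side of the frenulum of the tongue"; the second is on the right-hand vein. CV23 is on the front midline of the neck. Table 3 item 2a gives 10 or 12 insertions per session.

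**What is to be concluded.** The Introduction sets the aim as long-term efficacy compared with the placebo effect. Section 3 describes specific effects as arising from needling the acupoint with suitable manipulation, says a placebo is needed to recognize them, and states that "the efficacy of acupuncture could be confirmed if the results of the acupoint group prove superior to those of the NA control group".

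**The concern.** A sham comparison supports a claim about a specific effect only to the extent that the arms match on everything outside that effect. The plan names two intended differences: point location and manipulation for de qi. If the arms also differ in needle number, in bloodletting and in whether the mouth and neck are needled, a difference in AQ change at week 12 could come from any of these, and a two-arm trial cannot separate them.

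The unmatched parts are not incidental. Section 3 credits the tongue bloodletting with clinical efficacy of its own and CV23 with restoring speech. They are also the parts a participant is most likely to notice, and an eye patch does not hide a needle in the mouth.

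At stake is the meaning of a positive result. The sentence on identical procedures would lead a reader to attribute the whole difference to acupoint plus de qi.

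**Working it through.** **1. Reproduce the plan's insertion count** (Section 2.5.1 and Table 4).

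| Component | Insertions | Sham in Section 2.5.2 / Table 5 |
|---|---|---|
| HT5, bilateral | 2 | NA 1 |
| GB39, bilateral | 2 | NA 2 |
| DU20 | 1 | NA 3, partial |
| EX-HN1, four points | 4 | NA 3, partial |
| CV23, neck | 1 | none |
| EX-HN12 and EX-HN13, under the tongue | 2 | none |

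Retained needles: 2 + 2 + 1 + 4 + 1 = 10. With the two bloodletting insertions: 10 + 2 = 12. This reproduces the 10 or 12 of Table 3 item 2a for the acupoint arm.

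NA 3 is taken as a head site because Section 2.5 places sham points in the limbs and head, and NA 1 and NA 2 are beside limb points. It is a counterpart to the vertex needles only in the broad sense that both are on the head.

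**2. Control count.** The text gives no laterality for the sham sites and Figure 3 is not shown, so this is an assumption with a range.

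| Assumption | Control insertions | 12 ÷ control | 10 ÷ control | Over 12 sessions (active 144) |
|---|---|---|---|---|
| All single | 3 | 4.0 | 3.3 | 36 |
| NA 1 and NA 2 bilateral, NA 3 single | 5 | 2.4 | 2.0 | 60 |
| All bilateral | 6 | 2.0 | 1.7 | 72 |

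Three sites give at most 3 × 2 = 6, so neither 10 nor 12 can be reached in the control under any of these assumptions.

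**3. Matching by region.** Of the 12 active insertions, 4 have a limb sham, 5 (vertex) have a partial head counterpart, and 2 + 1 = 3 (tongue and neck), or 3/12 = 25%, have none.

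**4. The sentence against the list.** If identical procedures is taken literally to include tongue bloodletting in controls, Table 5 is incomplete and the control receives part of the active programme. If Table 5 is complete, de qi manipulation is not the only procedural difference. Either way the texts need reconciling.

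**5. Can the blinding check cover the gap?** Section 2.2 compares the proportions answering *yes* and lets a non-significant difference suggest sufficient blinding. Take 20 per group (Section 2.6) and, as an assumption for illustration, true proportions of 0.90 and 0.60.

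- SE under no difference: √(2 × 0.75 × 0.25 / 20) = 0.137
- SE under the difference: √(0.90 × 0.10 / 20 + 0.60 × 0.40 / 20) = 0.128
- Power ≈ Φ[(0.30 − 1.96 × 0.137) / 0.128] = Φ(0.25) ≈ 0.60

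Exact enumeration gives 0.62 for the uncorrected chi-square test and 0.49 for Fisher's exact test. A 30-point gap would thus be missed in roughly 38% to 51% of trials.

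A possible data set shows the same. With 16/20 against 11/20, the difference is 0.25, its SE is √(0.80 × 0.20 / 20 + 0.55 × 0.45 / 20) = 0.143, and the 95% interval is 0.25 ± 1.96 × 0.143, or −0.03 to 0.53. The chi-square p is 0.09, so the rule would pass it, although the interval allows a gap of more than 50 points.

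**The case against.** **The differences are partly the design.** Location and manipulation are the declared contrast, so omitting de qi in the control, or stimulating only the active limb needles, is no fault. This stands. Needle number and the tongue and neck components remain outside it.

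**The sentence on sameness follows a list of different sites.** It may mean technique, retention and schedule, and the sentences after it do equate retention and schedule. That softens it, but its only stated exception is de qi manipulation, and bloodletting is a procedure.

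**The head is covered.** Section 2.5.1 groups the tongue and neck points with the head, and NA 3 is on the head. That is a fair partial answer for the vertex needles. Table 4 places the other three insertions in the mouth and neck, where no sham is listed.

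**The programme framing already exists.** Section 2.1 compares the two groups as defined, and Section 3 speaks of an acupuncture programme. True, but the Introduction's aim and the inference in Section 3 go further.

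A reader might also infer more than the documents support:

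- *Blinding will fail.* Not shown. Participants are treated alone, told the treatments are effective and asked at week 4 what they believe they received. An oral needle reveals allocation only to someone who knows the other arm lacks one. It is a risk.
- *The control uses a different device.* Item 6b says participants "received sham acupuncture with a pragmatic placebo needle on a sham acupoint", but its next sentence says the needles are those of the acupoint group, and Section 2.5.2 and item 6a say real needles. This is an editorial slip.
- *The plan promises to prove an acupoint-specific effect.* Section 3 is conditional (could be confirmed) and speaks of the efficacy of acupuncture.

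**Conclusion.** The point holds in limited form. As written, the statement that procedures match apart from de qi does not agree with the listed control sites. Beyond the intended contrast, the arms differ in needle number (12 against 3 to 6, a ratio of 2 to 4, or 1.7 to 3.3 on retained needles alone) and in three tongue and neck insertions with no counterpart. The range rests on the unstated laterality of the sham sites; the direction does not.

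The randomized comparison remains valid for what was actually given: the whole programme against this reduced non-acupoint needling. What does not follow from superiority alone is that a specific acupoint effect has been separated from placebo, because needle number, bloodletting, neck needling and any difference in expectation remain alternative explanations. The blinding test, read by significance, is too weak at 20 per group to remove the last of these.

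**What to change.** No change to treatment is needed or proposed.

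1. Reconcile the sentences on identical procedures in Section 2.5.2 and Table 3 item 6b with the listed control sites. State every way in which the arms differ (sites, number of insertions, bloodletting, neck needle, manipulation), and give the laterality and insertion count of the control.
2. Restate the aim in the Introduction and the inference in Section 3 as the whole acupuncture programme against reduced non-acupoint needling, and say that superiority would support the programme.
3. In Section 2.2, report the between-arm difference in *yes* answers with its 95% confidence interval and interpret a positive primary result alongside it. Drop the reading of non-significance as sufficient blinding.
4. As an editorial correction, bring the placebo-needle phrase in item 6b into line with the sentence that follows it.

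The cost is a few sentences and a narrower claim. The primary analysis and the sample size are unaffected.
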